## Abstract

**Background::**

Catgut implantation at acupoints (CIA) is a subtype of acupuncture that has been widely used to treat simple obesity, but evidence for its effectiveness remains scarce. The aim of this study is to evaluate the efficacy and safety of treating simple obesity with CIA.

**Objective::**

This clinical trial aims to evaluate the effectiveness and safety of CIA used for treatment of simple obesity.

**Methods::**

This is a multicentre, randomized, parallel, sham-controlled clinical trial. A total of 216 patients with simple obesity will be recruited. They will be randomly assigned in a 1:1 ratio to either the CIA group or the sham control group. All treatments will be given once every 2 weeks. The primary outcome measure is the rate of waistline reduction. Secondary outcome measures are the rates of reduction of body measurements, including weight, body mass index (BMI), hipline, waist-hip-ratio (WHR) and body fat percentage (BFP), the changes in scores on scales, including the Impact of Weight on Quality of Life Questionnaire (IWQOL-Lite), Short Form 36 (SF-36), the Hospital Anxiety and Depression Scale (HAD) and the Self-Esteem Scale (SES), Outcomes will be evaluated at baseline and at weeks 4, 8, 12, 16, 28, and 40, respectively. All adverse events that occur during this study will be recorded. If any participant withdraws from the trial, an intention-to-treat analysis (ITT) will be performed.

**Conclusion::**

This is a randomized, sham-controlled trial of CIA treatment for simple obesity. The results of this trial will provide more evidence on whether CIA is efficacious and safe for treating obesity.

**Trial registration::**

ClinicalTrials.gov Identifier: NCT02936973. Registered on October 18, 2016.

## Introduction

1

Obesity is a type of chronic metabolic disease characterized by the excessive accumulation or abnormal distribution of fat in the body. Simple obesity is a type of obesity caused simply by energy intake exceeding energy consumption, in which other diseases or medical factors are excluded.^[1]^ With the development of the social economy and changes in lifestyle, the morbidity of obesity is increasing annually. According to the World Health Organization, the global overweight and obese populations, are predicted to reach more than 2.16 billion and 1.12 billion, respectively, by 2030.^[2]^ In 2008, the overweight and obese populations in China rose to 25.4% and 5.7%, respectively. In 2020, the obese population of China may be larger than that of America.^[3]^ Many studies^[4,5]^ have demonstrated that obesity is not only closely related to diabetes, polycystic ovary syndrome and other metabolic diseases but also an independent risk factor for hypertension, hyperlipidaemia, atherosclerosis and other metabolic diseases.

Current treatments for obesity mainly include drug treatments, operative treatments, changes in lifestyle (exercise, diet control), and traditional Chinese medicine (TCM). The use of pharmacological drugs for managing obesity remains controversial due to the side effects of these drugs.^[6,7]^ Gastrointestinal surgery is associated with high costs, risk of complications and strict indications. Acupuncture, which originated in China and is based on the framework of TCM, is an important alternative and complementary therapy for treating numerous diseases. As an available and affordable treatment, acupuncture is popular with many obese patients and has been widely used worldwide.^[8–10]^

As a subtype of acupuncture, CIA has developed rapidly over the last 60 years, and has been shown to have specific effects on chronic diseases, including simple obesity. Compared with manual acupuncture, the advantages of CIA lie in its persistence, improved patient compliance and superior long-term effects.^[11]^ A meta-analysis of CIA for obesity revealed that CIA is equivalent to drugs based on an assessment of pooled outcomes (improvement rate, weight loss, BMI, waistline, and hipline).^[12]^ Other recent meta-analyses^[13,14]^ indicate that treating obesity with CIA has a higher clinical effective rate than manual acupuncture and a rate equal to that of electro-acupuncture. Additionally, this treatment for treating obesity has positive effects on menopathy, hyperglycaemia, hyperlipidaemia, hypercholesterolemia and gastrointestinal disease, which has fewer adverse effects and more cost-effective.^[15]^ Treating obesity with CIA is likely to be applied more widely in the future. Although CIA has been used to treat obesity for several years, clinical trials have small sample sizes or other methodological limitations. Thus, a high level of evidence for CIA in the treatment of obesity must be obtained.

Most clinical trials investigating the treatment of simple obesity with CIA have compared CIA with manual acupuncture and electro-acupuncture,^[14]^ which led to 3 key questions: Is CIA absolutely effective and safe? Is the efficacy of CIA due to the effect of needling or blood-pricking and does this treatment for obesity result in a placebo effect? Does CIA have other effects (such as improving insulin resistance due to simple obesity and the quality life of obese people) in addition to helping obesity patients reduce their waistline measurements and lose weight?

The international gold standard remains to evaluate intervening measures with scientifically and normatively designed randomized, double-blind, sham-controlled trials.^[16]^ Due to the nature of CIA, it is not feasible to blind the acupuncturist during this study. However, all patients, statisticians and evaluators will be blind. To answer the above 3 questions, we wish to design a randomized, parallel, multicentre trial at 3 sites in China with an appropriate sample size using sham control to demonstrate its safety and efficacy.

## Methods/design

2

### Ethics approval

2.1

The study design complies with the guidelines of the Declaration of Helsinki (Version Edinburgh 2000), meets medical ethics requirements and has been approved by the Ethics Committee of Hubei Provincial Hospital of Traditional Chinese Medicine (HBZY2016-C20–01), Dongzhimen Hospital Beijing University of Chinese Medicine (DZMEC-KY-2017–15) and the First Hospital of Hunan University of Chinese Medicine (HN-LL-KY-2017–001–01). The study has been registered under the identifier NCT02936973 at Clinical Trials.gov.

### Study/design

2.2

This randomized, controlled, two-arm clinical trial will be conducted at Hubei Provincial Hospital of TCM, Dongzhimen Hospital Beijing University of Chinese Medicine and the First Hospital of Hunan University of Chinese Medicine. This study includes the following scheduled events: a treatment period of 16 weeks and a follow-up period of 24 weeks. The total study period will be 40 weeks. During the baseline period, each participant should keep a diet and exercise diary for 2 weeks before randomization. The diary will be kept throughout the research cycle if the participant is eligible for the study. The patients will be randomly selected for the CIA group (n = 108, expected) or the sham control group (n = 108, expected). CIA will be administered once every 2 weeks. All patients will receive 16 weeks of treatment. Each patient's blood pressure, heart rate, routine blood parameters and hepatorenal function will be tested before randomization and at the end of treatment. Body measurements of obese people (waistline, weight, BMI, et al) should be conducted and the IWQOL-Lite,^[17]^ SF-36,^[17]^ HAD,^[18,19]^ and SES^[20]^ will be completed throughout the study. Figure 1 provides a flow chart for the study.

**Figure 1 F1:**
[figure not shown]
Flowchart for the trial.

### Participants

2.3

#### Diagnostic criteria

2.3.1

Patients must meet the diagnostic criteria in the guideline of The Asia-Pacific perspective: redefining obesity and its treatment.^[21]^ According to the guideline, the standard for Asian adult obesity is BMI≥25, whereas, for European adults, obesity is defined by BMI≥30. The difference is due to racial and epidemiologic diversity. Owing to this study will be conducted in China, the Asian obesity standard is chosen. Because early treatment is superior when TCM is used, 1 inclusion criterion for this study is a BMI between 25 and 30.

#### Inclusion criteria

2.3.2

1.Diagnosed with simple obesity^[21]^2.Age: 18–453.BMI: 25≤BMI<304.Waistline: males≥95 cm; females≥85 cm5.Smokers have not changed their smoking habits for at least 2 months^[22]^6.Willing to accept the above-described intervention methods

#### Exclusion criteria

2.3.3

1.Endocrine disease (such as polycystic ovary syndrome, Cushing's disease, or hypothyroidism)2.Gestational diabetes or uncontrolled hypertension (SBP≥160 mm Hg; DBP≥100 mm Hg),^[23]^ or lung, heart, liver or kidney disease3.Nervous system disease or mental disorders, history of hospitalized depression, 2 instances of paralepsy or suicidal tendencies^[24]^4.History of clinical diagnosis of an eating disorder,^[24]^ such as bulimia,^[25]^ cynorexia or anorexia; weight changes greater than 5 kg in the previous 3 months5.History of weight loss with surgery^[26]^ or a history of post-operative adhesion^[25]^6.History of taking taken drugs with a known influence on weight or appetite in the previous 3 months, such as diet pills, corticosteroids, anti-depressants, diazepam, nonselective body antihistamines, nicotine replacements, or hypoglycaemic drugs or planning to give up smoking and drinking7.Pregnancy, lactation, or planning to become pregnant within 40 weeks8.Received CIA9.Participated in clinical research on obesity in the previous 3 months^[27]^10.Protein allergies and scars11.Skin disease such as eczema and psoriasis12.Coagulation disorders, or use of warfarin, heparin or other anticoagulant drugs13.Not able to cooperate or maintain the treatment during the study period

#### Withdrawal from the study

2.3.4

1.A specialist physician at each centre responsible for evaluating serious adverse effects during the study decides to withdraw the patient from the study2.Severe complications or other severe diseases necessitating emergency measures3.Participants decision to withdraw from the study

#### Recruitment

2.3.5

We will design a public recruitment advertisement and recruit any patients who meet the criteria through newspapers, posters, WeChat or the Internet. The doctor will determine whether the patients are eligible to participate in this study. All patients will be given sufficient time to decide whether to participate in the trial. A voluntarily signed, written, the informed consent form will be obtained from each participant. It provides the patients with details about related clinical research in language that the patients or their legal representatives can understand, including descriptions of the research objective, the research method and the process (including treatment measures, grouping, tests, potential benefits to the patients and potential risks and inconvenience that the patients may endure).

#### Safety assessment

2.3.6

The safety assessment of CIA will include 3 aspects. First, a general physical examination that includes blood pressure, heart rate, routine blood, and hepatorenal function will be used as a safety index and be conducted before randomization and at the end of treatment. Besides, the incidence of adverse events, such as severe pain, allergic reaction, syncope, local induration, local haematoma, and local infection, will be recorded. The Visual Analogue Scale (VAS) will be used to assess the perception of pain due to CIA in the study.

### Intervention

2.4

This is a placebo-controlled, double-blind, randomized trial, with a treatment of 16 weeks and a follow-up of 24 weeks. Each session will last for close to 10 minutes once every 2 weeks. All participants will be treated continuously for 16 weeks. The design of the study is consistent with the Standards for Reporting Interventions in Controlled Trials of Acupuncture (STRICTA) guidelines^[28]^ and the guidelines for clinical research on acupuncture (WHO Regional Publication, Western Pacific Series No.15, 1995). We will formulate standard operating procedures (SOPs) to ensure the standards and quality of the study. CIA will be performed by qualified TCM doctors with at least 3 years of clinical acupuncture experience.

#### CIA group

2.4.1

Treatment measures for the CIA group will include CIA and lifestyle modification. The CIA prescription was selected by 3 steps: first, the domestic and overseas literature from over the last 30 years on CIA for curing simple obesity was reviewed. Based on complex network technology, the rules for selecting acupoints for treating simple obesity with CIA were analyzed. Subsequently, the aetiology and pathogenesis of obesity will be discussed by professional acupuncturists to modify the prescription according to basic theories of TCM. After the CIA, the stimulation will last for about 2 weeks. Two groups of acupoints will ultimately be selected for alternative treatment once every 2 weeks. The acupoints of Groups A and B are one to one in the same regions of the body. Group A includes Zhigou (TE6), Tianshu (ST25), Weishu (BL21), Zhongwan (CV12), and Zusanli (ST36); Group B includes Quchi (LI11), Huaroumen (ST24), Pishu (BL20), Shuifen (CV9), and Fenglong (ST40). There will be 8 treatments throughout the study.

##### Application of catgut embedding

2.4.1.1

The instruments that will be used in the study include disposable embedding needles (#9#, Zhenjiang Gaoguan Medical Appliance Factory, Jiangsu, China), absorbable catgut sutures (000, Shandong Boda Medical Supplies Co. Ltd., Shandong, China), and disposable embedding aids (Yangzhou City Dragon Tiger Medical Instrument Factory, Jiangsu, China). CIA will be performed for patients assigned to the CIA group according to the Operation Standard for Acupuncture, Part 10: Catgut Implantation at Acupoints (GB/T 21709.10–2008). The doctors should wash both hands with soap, flush with running water and wipe with 75% ethyl alcohol and 0.5% iodophor before putting on sterile gloves. The operation site should be disinfected with 0.5% iodophor in a circular pattern from the centre outward. When the acupoints and the surrounding skin have been disinfected, an absorbable catgut suture of an appropriate length will be placed at the front end of the trocar before the stylet is connected. The proposed acupoint will be fixed with the thumb and index finger of one hand, and the needle will be inserted into the acupoint with the other hand to the required depth. Appropriate twirling, lifting and thrusting will be applied. When a needling sensation occurs, the stylet will be pushed while the tube is withdrawn, which will embed the absorbable catgut suture into the muscular layer or subcutaneous tissue of the acupoint. Then, the acupoint will be pressed with a dry cotton ball to avoid bleeding after the needle is withdrawn. The patient will be told to keep the skin at the acupoint dry for 3 days after treatment.

##### Lifestyle modification

2.4.1.2

The lifestyle modification treatment will be designed by experienced nutritionists. First, the basal metabolic rate (BMR) of the patient will be calculated using the formula suggested by the FAQ/WHO. Second, the difference between the daily dietary caloric intake and calories consumed during exercise will be calculated according to the BMR, namely dietary caloric intake - calories consumed during exercise ≤ basal metabolic rate. Finally, a proper diet and exercise treatment will be designed for the patient based on the above difference. The dietary distribution will be designed according to the Chinese Dietary Guidelines approved and issued by the Standing Council of the Chinese Nutrition Society. The 3 nutrients included in the total energy should be in the following proportion: carbohydrates account for 55% to 65%, oil or fat accounts for 20% to 30%, and protein accounts for 15%. These will be distributed proportionally among 3 meals (breakfast 30%, lunch 40%, and dinner 30%) to distribute the energy throughout the day. In terms of daily exercise, brisk walking, jogging and swimming could be performed under the guidance of the physician. During the treatment, a diet and exercise diary will be distributed to the patients,^[29]^ and detailed guidance concerning their diet and exercise will be provided using an instruction manual for dining and sports. The patients should be encouraged to track their diet and exercise at least 4 days per week (3 days on weekdays and 1 day on the weekend).^[30]^ The meals and excise will be quantified using calories in the diary. The diet and exercise diary will be collected from each patient at baseline and at weeks 4, 8, 12, 16, 28, and 40 to estimate the intake of nutrients and to monitor the diet and amount of exercise. During the treatment, the patients will receive 16 consultations with a nutritionist. In addition, social tools (QQ and WeChat) will be used to build a social network among the doctors and patients during the 16 weeks of treatment and the 24 weeks of follow-up.

#### Sham control group

2.4.2

The treatment in the sham control group will include sham stimulation and lifestyle modification. Acupoints for the sham control group are located 1 cun (≈20 mm) from the points used for the CIA group, and the position of sham acupoints cannot be located in any real acupoints and meridians of the body. The operation process will be similar to the one used with the CIA group. The patients will lie on their backs to expose the implantation locations. The positions will be located and disinfected with iodine. An empty needle will be pushed into the chosen position, to a depth equivalent to that used for CIA group. To ensure blinding, all patients will undergo the scheduled treatment. The physicians cannot communicate with the patients during the operation. The lifestyle modifications of the sham control group will be equivalent to those of the CIA group. The locations of CIA group and the sham control group are detailed in Figure 2. Figure 3 shows the difference between CIA group and sham CIA group. (A) A thread- embedding needle will be inserted in the location of acupoints. The catgut suture will be pushed into the tissue using the stylet. (B) A thread- embedding needle will be inserted into sham point, and catgut will be not embedded. (1.stylet 2.trocar 3.thread- embedding needle 4. surgical suture).

**Figure 2 F2:**
[figure not shown]
Acupoints for catgut implantation and places for control stimulation.

**Figure 3 F3:**
[figure not shown]
The difference between CIA group and sham CIA group.

### Outcome measurements

2.5

#### Primary outcome

2.5.1

The primary outcome measurement of this study will be the rate of waistline reduction compared with the baseline. Evaluations will be conducted at weeks 0, 4, 8, 12, 16, 28, and 40. The waistline is the simplest and most practical index to measure the amount of fat accumulated in the stomach (central obesity). The distribution of fat in the body, especially the accumulation of fat in the stomach, has a close relationship with obesity-related diseases.

#### Secondary outcome measurements

2.5.2

1.The reduction rate of weight, BMI, hipline, WHR, and BFP will be evaluated at baseline, and at weeks 4, 8, 12, 16, 28, and 40. These indicators are related to the shapes of obese people. High indicators suggest an increased risk of obesity-related diseases.2.Changes in the SF-36, HAD and SES scores will be evaluated at baseline, and at weeks 16 and 40, and the IWQOL-Lite will be evaluated at baseline and at weeks 4, 8, 12, 16, 28, and 40. The SF-36 and IWQOL-Lite will be used to evaluate changes in the quality of life of the obese patients. The HAD and SES will be used to evaluate changes in the psychological status of the 216 obese patients.

### Sample size estimation

2.6

Based on a review of the literature, clinical experience and discussion among clinical experts, we anticipated 7% waistline reduction at 16 weeks in the CIA group and 2% reduction in the sham CIA group. Eighty six participants per group was required based on:

1.a mean clinically relevant difference of 5% (2% reduction in the sham CIA group), with a pooled standard deviation (SD) of 8.1%;2.2-sided at 5% and 1- at 80%.

Assuming 20% attrition rate, we plan to enrol a total of 216 participants (108 per group).

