### Randomization and blinding

2.7

This trial will use centralized block randomization generated by a computer (using the professional statistical software SAS 9.1.3 to assign a randomized group number to allocate the treatment programme to be completed). The randomization programme and the various parameters established during the process are collectively known as the blind code, which will be sealed with the signature of the person who created the randomization programme and will be maintained by a special research group administrator at Hubei Provincial Hospital of TCM who will not participate in the project. Each eligible patient will receive a group number according to the inclusion sequence and will be assigned to the treatment programme with the corresponding number, which will remain the same throughout the trial. Number jumping or selecting is not allowed. Each number is associated with an emergency envelope with the corresponding number, which will be maintained by a principal researcher in each trial unit.

Blinding will be conducted for all patients, evaluators and statisticians. During the trial, only the persons performing the CIA will be aware of the patient's group assignment. The patients will be assigned in a 1:1 ratio to either the CIA group or the sham control group, which will be called A and B, respectively, in the treatment record report. All information will be locked in the database until the statistical analysis is conducted. This study will utilize an independent treatment room and make appointments with the patients directly to ensure that patients from different groups do not communicate.

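### The sample size does not follow from its stated inputs: they need 42 or 43 participants per group, not 86

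*Protocol article*

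**What the plan says.** Section 2.6 (Sample size estimation) gives the full chain from assumptions to enrolment.

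- Expected means: "we anticipated 7% waistline reduction at 16 weeks in the CIA group and 2% reduction in the sham CIA group".
- Difference and spread: "a mean clinically relevant difference of 5% (2% reduction in the sham CIA group), with a pooled standard deviation (SD) of 8.1" percent.
- Error rates: two-sided 5%, and 80% for the power. The Greek letter is lost in the text, but 80% can only be the power here.
- Result: "Eighty six participants per group was required based on" these inputs.
- Enrolment: "Assuming 20% attrition rate, we plan to enrol a total of 216 participants (108 per group").

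Section 2.7 fixes equal allocation: "The patients will be assigned in a 1:1 ratio to either the CIA group or the sham control group". The abstract repeats the total of 216, and section 2.2 repeats 108 per group.

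**The concern.** A difference of 5 with an SD of 8.1 is a standardised effect of 5/8.1 = 0.62. An effect of that size needs a little over 40 participants per group at 80% power, about half the number given. The article presents 86 per group as the consequence of the printed inputs, so the reader should be able to reproduce it.

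Two things are at stake. If the printed inputs are right, the trial enrols about twice as many people as its own assumptions call for, and everyone enrolled is needled, because the sham group receives an empty needle at the same depth (section 2.4.2). If an input is misprinted, the power at the 5-point target is unknown, because the difference, SD or power actually used is not on the page.

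**Working it through.** **Inputs** (section 2.6, with allocation from section 2.7): difference Δ = 7 − 2 = 5 percentage points; SD σ = 8.1; two-sided α = 0.05 (z = 1.960); power 0.80 (z = 0.842); allocation 1:1; attrition 20%.

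**1. The plan's own figures.** The attrition step reproduces: 86 / (1 − 0.20) = 107.5, so 108 per group and 216 in total. The 86 per group that enters it does not reproduce, as the next step shows.

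**2. Sample size from the stated inputs.**

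- Normal approximation: n per group = 2 (z₁₋α/₂ + z₁₋β)² (σ/Δ)² = 2 × (1.960 + 0.842)² × (8.1/5)² = 2 × 7.85 × 2.624 = 41.2, so 42 per group and 84 in total.
- Two-sample t-test (noncentral t): 42.18, so 43 per group and **86 in total**. Power is 80.8% at 43 per group.

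The stated per-group number is exactly twice the t-test answer: 86 / 43 = 2.0.

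**3. What 86 per group delivers.**

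- Standard error of the difference: 8.1 × √(2/86) = 1.235.
- Power for 5 points, normal approximation: Φ(5/1.235 − 1.960) = Φ(2.09) = 98.2%. By the t-test it is 98.1%.
- With 108 per group and no loss, power is 99.5%.
- Detectable difference at 80% power: 2.802 × 1.235 = 3.46 points (3.48 by the t-test).
- SD at which 86 per group gives 80% power for 5 points: 5 / (2.802 × √(2/86)) = 11.7 (11.6 by the t-test).

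**4. Enrolment from the stated inputs.** 43 / 0.80 = 53.75, so 54 per group and 108 in total. The normal approximation gives 42 / 0.80 = 52.5, so 53 per group and 106 in total.

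**5. Other readings tried** (n per group; where two numbers are given, normal approximation then t-test):

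| Variant | n per group |
|---|---|
| One-sided 5%, 80% power | 33; 34 |
| Two-sided 5%, 90% power | 56; 57 |
| Two-sided 5%, 95% power | 69; 70 |
| Two-sided 5%, 98% power | 85; 86 |
| 5% split over six post-baseline visits, 80% power | 64 (normal) |
| SD multiplied by √2 (11.46) | 83; 84 |
| 7% and 2% treated as proportions | 269 (308 with continuity correction) |

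Only 98% power reaches 86, and that contradicts the stated 80%. The √2 variant comes close but contradicts the statement that 8.1 is the pooled SD.

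**The case against.** The strongest case on the other side accepts the arithmetic and disputes what is drawn from it.

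- **The cause is not established.** Section 2.6 names no test. The total is 86 only by the t-test and is 84 by the normal approximation, and 98% power or an SD near 11.6 would also lead to 86 per group. This stands: the total-read-as-per-group explanation is the likeliest, not a demonstrated fact. The mismatch does not depend on it.
- **There is one error, not two.** The step from 86 to 108 is right, and all mentions of 108 and 216 agree. This also stands. The enrolment is wrong only in that it inherits the 86.
- **The direction is harmless to the primary comparison.** If the printed difference and SD are right, the trial has more power than claimed; if the SD was really near 11.6, then 216 is about right and only the text is wrong. The type I error is unaffected. This is fair, but it leaves open a possible doubling of the number of people needled.
- **The target effect is stated.** It is 5 points, so the target itself is not hidden. What cannot be known is the power at that target or the SD behind it.
- **Halving enrolment could do damage.** If the true SD is larger than printed, 54 per group would be too few. Safety is also a stated objective, and adverse-event incidence is compared between groups (section 2.10), a comparison that loses precision at half the size. This stands, and it makes a reduction conditional on confirming the inputs.

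Nothing in the article supplies a reason for the doubling. It gives no multiplicity split (tests are at a two-sided 5%), no design effect for centre and no interim analysis, and attrition is added afterwards. Adjustment for baseline in the planned mixed model would usually lower the required number. Condensation of a fuller protocol does not explain it either, because the article prints the inputs and the result side by side.

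**Conclusion.** The concern holds. The inputs in section 2.6 need 42 or 43 evaluable participants per group; the article states 86. At 86 per group the power for a 5-point difference is about 98%, and the 216 enrolment is twice the 108 that the inputs and 20% attrition imply.

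This rests on a two-group comparison of mean percentage reduction at week 16, equal allocation, a common SD of 8.1 and no unstated adjustment. The normal approximation and the t-test differ by one participant per group, so the choice of method does not matter. Which number is wrong (the 86, the SD, the difference or the power) cannot be settled from the document. If the printed inputs are right, the consequence is over-enrolment and not loss of power.

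**What to change.** Rewrite section 2.6 so that the number follows from what is printed, and name the test or formula used. The authors should go back to the original calculation and choose accordingly:

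1. **Inputs right, enrolment kept at 216.** State that 86 evaluable per group gives about 98% power for 5 points at SD 8.1, or 80% power for about 3.5 points, and give the reason for the larger number.
2. **A different input was used.** Print it. For example, an SD of about 11.6 would give 86 per group at 80% power for 5 points.
3. **Inputs confirmed and enrolment still open.** Correct to 43 evaluable and 54 enrolled per group (108 in total), and change the abstract and section 2.2 to match. Take this route only after the SD and difference have been checked and the loss of precision for the adverse-event comparison has been weighed.

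The first two cost one paragraph and no patients. The third halves enrolment and is not needed to correct the error.
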